#### Primary analysis

Cox regression is planned to assess the effect of the treatment group on Hazard Ratios (HR) and to adjust for prognostic factors for recurrence of LBP, if these are unbalanced between groups despite randomisation. Kaplan–Meier survival plots will be constructed to visually display survival curves, with patients censored on the day of their last successful follow-up, or when the participant was identified to have the event (i.e. recurrence), whichever occurs first. HR and median survival times with 95% CIs will be reported. The effect of including the variables that were used for the stratified randomisation as strata in these analyses will also be assessed (i.e. clinician versus community referral and the number of previous episodes (up to 2 versus > 2 episodes)).

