#### Sample size and randomisation

A sample size calculation indicated that 349 participants per group (698 total) would provide 80% power to detect a 25% relative reduction in recurrence rates of *activity-limiting LBP* (i.e. primary outcome) in the intervention group, compared to the control group. We used a conservative estimate of 30% recurrence rate at 12 months in the control group, a rate observed in previous work by Stanton et al. [19] A 25% relative reduction (from 30 to 22.5%) is large enough to have important public health implications for such a simple intervention. Specifications include a two-sided log-rank test, Type-I error = 0.05, 24-month accrual period, and 12-month follow-up period. Sample size calculations allowed for 1% loss to follow-up per month.

Randomisation to intervention or control was conducted using a pre-generated schedule and allocation concealment was ensured at the patient level. Randomisation used randomly permuted blocks of 4, 6 and 8 and participants were stratified by history of > 2 previous lifetime episodes of LBP (known to be a prognostic factor for recurrence) [3], and recruitment from the community versus clinician referral.

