### Statistical analysis

#### Analysis principles

All analyses will be conducted using R software (version 4.2.2 or above) or STATA (version 17.0 or above). Analyses of the primary and secondary outcomes will be conducted by a statistician (member of the trial team), taking no part in participant recruitment or data collection. Analyses will follow intention-to-treat principles, with all participants analysed according to their randomised allocation. A masked sample of the data will first be used to trial and confirm statistical procedures. Next, the fully masked dataset will be used, with data interpretation occurring prior to unblinding of group allocation. There is no intention to conduct interim analyses.

Categorical variables will be summarised by frequencies and percentages. Continuous variables will be reported using standard measures of central tendency and dispersion, either mean and standard deviation (SD) or median and interquartile range, depending on the shape or skewness of the data. A *p*-value < 0.05 will be considered statistically significant. A 95% confidence interval (CI) will be reported to aid the interpretation of precision and the clinical importance of findings.

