##### Economic evaluation analyses

The economic evaluation will be conducted from the societal perspective as the primary analysis, whilst the Australian health system perspective will be used for sensitivity analyses. The time horizon of the economic analysis is 12 months.

For the economic evaluation, missing cost and effect data will be imputed using multivariate imputation by chained equations with predictive mean matching [21]. The imputation model will include variables differing between groups at baseline as well as those predicting the missingness of follow-up cost and effect data. Cost and effect differences will be estimated using seemingly unrelated regression analyses, in which two regression equations are modelled simultaneously and cost and effect differences are adjusted for their possible correlations through correlated error terms. Cost and effect differences will be adjusted using the same covariates as the primary effectiveness analyses, in addition to work status and baseline utility values for QALYs [22]. To handle the right skewed nature of cost data, uncertainty surrounding cost differences will be estimated using bias-corrected and accelerated bootstrapping (5000 replications) [23].

Incremental cost-effectiveness ratios (ICERs) will be calculated by dividing the between-group difference in costs by the between-group difference in effects (i.e. cost per recurrence prevented, and cost per QALY gained). The uncertainty surrounding ICERs will be estimated using bootstrapping as well (5000 replications) and graphically presented on cost-effectiveness planes. Cost-effectiveness acceptability curves will be estimated to show the probability of the intervention being cost-effective for a range of willingness to pay (i.e. maximum amount decision-makers are willing to pay per unit of effect gained). Sensitivity analyses will be performed to assess the robustness of the results based on a complete-case analysis and an analysis from the Australian health system perspective.

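### The primary Cox model adjusts only for unnamed prognostic factors that turn out unbalanced, and leaves the randomisation strata to an add-on check, so the headline hazard ratio is not fixed and precision is lost

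*SAP article*

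**What the plan says.** The Primary analysis section of the SAP article is the only place that specifies the primary model. Cox regression is planned to estimate the treatment hazard ratio and "to adjust for prognostic factors for recurrence of LBP, if these are unbalanced between groups despite randomisation". Of the randomisation factors it says: "The effect of including the variables that were used for the stratified randomisation as strata in these analyses will also be assessed".

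The section on sample size and randomisation reports that "participants were stratified by history of > 2 previous lifetime episodes of LBP (known to be a prognostic factor for recurrence"; the second stratification factor is community recruitment versus clinician referral. No other variable is called prognostic for recurrence.

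The open covariate set is used elsewhere. Any recurrence and care-seeking recurrence receive a survival analysis analogous to the primary one. For the economic evaluation, "Cost and effect differences will be adjusted using the same covariates as the primary effectiveness analyses", with work status added, and baseline utility for QALYs.

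On safeguards, the Analysis principles section says that "the fully masked dataset will be used, with data interpretation occurring prior to unblinding of group allocation". The Blinding section says the code is broken only after the authors agree on the interpretation.

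**The concern.** In a randomised trial a baseline difference between arms is chance. What adjustment gains depends on how strongly a variable predicts recurrence, not on whether it happens to differ in this sample. A trigger based on imbalance therefore selects covariates on the wrong property.

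Three things follow.

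- The primary model is not uniquely defined. It could be unadjusted, or adjusted for some subset of unnamed factors, with no stated threshold and no stated headline hazard ratio. Because the Cox hazard ratio is non-collapsible, these versions also estimate different quantities.
- The committed model omits the one factor that the SAP calls prognostic. Randomisation was stratified on it in permuted blocks, so it is unlikely ever to look unbalanced and trigger its own inclusion.
- The same open set feeds two secondary recurrence outcomes and the cost and effect models.

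**Working it through.** **1. The plan's own figure.** The inputs, from the section on sample size and randomisation, are 30% versus 22.5% recurrence at 12 months, 80% power, and a "two-sided log-rank test, Type-I error = 0.05, 24-month accrual period, and 12-month follow-up period", with 1% loss per month.

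- Hazard ratio under exponential survival: ln(0.775)/ln(0.70) = 0.715.
- Events by the Schoenfeld formula: 279.
- Event probabilities under uniform accrual, with loss: 0.4486 (control) and 0.3509 (intervention).
- Per arm: 279/(0.4486 + 0.3509) = 349.0, with power 80.1% at 349.

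The stated 349 per group reproduces. The calculation contains no covariates, so this point does not change it.

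**2. What the documents do not supply.** They give no covariate strengths and no imbalance threshold. All figures below rest on assumptions. Imbalance in steps 3 and 4 means |z| > 1.96. Compare power within a scenario only: the absolute level depends on how covariate heterogeneity was added to the planning hazards.

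**3. Power at the design effect**

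| Assumed scenario | Unadjusted | Imbalance-triggered | Fixed model |
|---|---|---|---|
| A: 698 patients; >2 episodes HR 2.0 at 60% prevalence; one further covariate HR 1.5 per SD; 5,000 runs; fixed model = strata + covariate | 75.8% | 76.2% | 81.3% |
| B: 701 patients; 5 covariates, log HR 0.25 per SD; 1,500 runs; fixed model = all 5 | 69.0% | 69.9% | 76.2% |
| C: 701 patients; 10 covariates, log HR 0.20 per SD; 1,500 runs; fixed model = all 10 | 66.5% | 67.3% | 74.8% |

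- Triggered minus unadjusted: 0.4, 0.9 and 0.8 points.
- Fixed minus triggered: 81.3 − 76.2 = 5.1; 76.2 − 69.9 = 6.3; 74.8 − 67.3 = 7.5 points.
- Monte Carlo standard error of a single power figure at 1,500 runs: √(0.7 × 0.3/1,500) ≈ 1.2 points. The comparisons within a scenario use the same simulated trials, so their differences are steadier than that.

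In B and C the trigger fired for at least one covariate in only 22–24% and 39–40% of trials. Otherwise the result is simply the unadjusted one, which is why the rule gains almost nothing.

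**4. Type I error under the null.** The triggered rule, applied mechanically, rejected in 4.6% (A), 5.1% (B) and 3.7% (C) of trials. If an analyst could instead report whichever of the unadjusted, triggered and full models was significant, rejection was 8.1% (B) and 6.2% (C), against 5.5% and 4.1% for the unadjusted test in the same runs. That is the cost of unconstrained discretion, not of the trigger.

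**5. How much comes from the strata alone.** A separate run of 4,000 trials with A's covariate strengths, with marginal risks set to 30% and 22.5%, gave 76.7% unadjusted, 78.0% stratified only and 82.0% stratified plus covariate. The strata add 78.0 − 76.7 = 1.3 points; the further covariate adds 82.0 − 78.0 = 4.0.

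**The case against.** The strongest reply is that this is ordinary under-specification with real safeguards. The trigger refers to baseline differences, not outcomes. Procedures are tried on a masked sample first, interpretation is settled before the code is broken, and the Conclusion promises that deviations will be reported. The randomisation strata are named and will be examined. The power loss rests on assumed covariates, and most of it comes from a hypothetical one. The economic models also carry some fixed terms.

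Most of this stands and sets the severity. It does not remove the point. Masking hides which coded arm is which, but not the size of the difference between them under each covariate set, and the SAP does not say the covariates are locked before outcomes are seen. Assessing the strata in addition does not put them in the primary model.

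Three stronger readings are tempting, and the documents do not support them.

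- *The rule inflates type I error.* Step 4 shows that a mechanical trigger does not. Inflation needs an analyst who picks the significant model, and the SAP does not license that.
- *Some covariate is almost bound to look unbalanced.* Screening 24 independent Table 1 characteristics at the 5% level would give 1 − 0.95^24 = 71%. The SAP contains no such screen, limits adjustment to prognostic factors, and lists several plainly correlated rows, such as three DASS-21 subscales.
- *The unadjusted hazard ratio is biased towards 1.* The mean values of 0.73 unadjusted and 0.71 adjusted in scenario A reflect marginal and conditional estimands, not bias.

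**Conclusion.** The point holds as a should-fix. The SAP states a rule for the primary model that chooses covariates by chance imbalance, leaves the headline hazard ratio undefined, and keeps the randomisation factors out of the committed model. The validity of the test is not at risk if the rule is applied mechanically, and the sample size is unaffected.

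The size is modest: roughly 1 to 2 points of power from the strata alone, and about 5 to 8 points if further strong prognostic covariates are fixed as well. Both ranges depend on assumed covariate strengths and, for the triggered rule, an assumed threshold. With weaker covariates the gain would be smaller. That the primary model is not uniquely defined does not depend on any of these assumptions.

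**What to change.** In the Primary analysis section, delete the imbalance condition. Before unmasking, state that:

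- the primary hazard ratio comes from one Cox model that includes, or is stratified by, the two randomisation factors (up to 2 versus more than 2 previous episodes; community versus clinician referral);
- any further baseline covariates form a short list, named in advance on prognostic grounds with their functional form, and are used whatever the observed balance;
- the unadjusted hazard ratio is supportive, and any imbalance-driven adjustment is a sensitivity analysis.

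Use the same fixed list for any recurrence and care-seeking recurrence. In the economic models, use it alongside the work status and baseline utility terms already specified.

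The cost is wording only. The stratification factors and the Table 1 variables are already collected, the sample size does not change, and the SAP places database lock at an estimated September 2023, after the plan was written.

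### The lead Cox model leaves out the two factors that stratified randomisation; making the stratified model primary would be a small gain at no cost

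*SAP article*

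**What the plan says.** The Sample size and randomisation section states that "participants were stratified by history of > 2 previous lifetime episodes of LBP (known to be a prognostic factor for recurrence"), with the second stratification factor being "recruitment from the community versus clinician referral". It adds: "Randomisation used randomly permuted blocks of 4, 6 and 8".

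The Primary analysis section plans a Cox regression for treatment group, and "to adjust for prognostic factors for recurrence of LBP, if these are unbalanced between groups despite randomisation". The stratification factors come at the end of that section: "The effect of including the variables that were used for the stratified randomisation as strata in these analyses will also be assessed". The section names both factors there, with the cut-point for previous episodes.

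Two later sections depend on this choice. Under Effectiveness outcome analyses, any recurrence and care-seeking recurrence are to be analysed in the same way as the primary outcome. Under Economic evaluation analyses, "Cost and effect differences will be adjusted using the same covariates as the primary effectiveness analyses".

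**The concern.** The design treats previous episodes as important enough to stratify on, but the lead analysis does not use that information. Two consequences follow.

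- **The covariate rule does not bring the factors in.** A factor enters the lead model only if it is unbalanced. Stratified permuted blocks are meant to prevent imbalance on exactly these two factors, so the one factor the plan names as prognostic is among the least likely to be admitted.
- **Some power is given up.** When a prognostic stratification factor is omitted from a Cox model, the treatment hazard ratio moves toward 1 and the test becomes slightly conservative. The trial was sized for 80% power and randomised 701 against a requirement of 698, so there is little slack.

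The same choice carries over to the two other recurrence outcomes and, through the shared covariate set, to the economic models.

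**Working it through.** **1. Reproduce the plan's own figure.** The Sample size and randomisation section gives 12-month recurrence of 30% and 22.5%, a two-sided log-rank test at 0.05, 80% power, 24 months of accrual, 12 months of follow-up and 1% loss per month. Exponential survival and uniform accrual are assumed.

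- Monthly hazards: −ln(0.70)/12 = 0.0297 (control) and −ln(0.775)/12 = 0.0212 (intervention).
- Hazard ratio: ln(0.775)/ln(0.70) = 0.7146.
- Events (Schoenfeld): 4 × (1.960 + 0.842)² / (ln 0.7146)² = 278.1, rounded up to 279.
- Probability of an observed event, with k = λ + 0.01005 (loss hazard −ln 0.99): (λ/k) × [1 − (e^(−12k) − e^(−36k))/(24k)] = 0.4486 (control) and 0.3509 (intervention), mean 0.3997.
- N = 279/0.3997 = 698, which matches "349 participants per group (698 total) would provide 80% power".

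The section mentions no stratification of the log-rank test.

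**2. Compare unstratified and stratified log-rank tests by simulation.** Each simulated trial had 698 participants, permuted blocks of 4, 6 and 8 within the four strata, and the accrual, follow-up and loss above. The baseline hazard was set so that overall control recurrence at 12 months is 30%. Assumed, because the plan does not give them: 70% of participants in the higher-risk level of previous episodes, 20% in the higher-risk level of recruitment source, and the factor hazard ratios in the table. There were 4,000 runs per cell.

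| Assumed factor HRs (episodes, source) | Power, unstratified | Power, stratified | Type I error, unstratified |
|---|---|---|---|
| 1 and 1 | 80.5% | 80.1% | 4.7% |
| 1.5 and 1.2 | 79.3% | 79.7% | 4.7% |
| 2 and 1.5 | 78.2% | 79.6% | 4.4% |
| 3 and 2 | 74.9% | 79.8% | 4.1% |

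Type I error of the stratified test was 4.8% to 5.4%. Simulation error is √(0.8 × 0.2/4000) = 0.6 points for power and √(0.05 × 0.95/4000) = 0.3 points for type I error. The first two rows are therefore indistinguishable from no difference.

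A second set of 5,000 simulated trials per scenario assumed 60% with more than 2 episodes. It gave 79.2% against 79.6% for a factor hazard ratio of 1.5, and 78.4% against 80.0% for 2.0. The last gap, 1.6 points, is the upper end of the moderate range.

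**3. See where the loss arises.** Cox models were fitted under the step 2 assumptions, 1,000 runs per cell, with a true hazard ratio of 0.7146:

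| Assumed factor HRs | HR, unstratified | HR, stratified | Model SE of log HR, unstratified | Model SE of log HR, stratified |
|---|---|---|---|---|
| 1.5 and 1.2 | 0.721 | 0.718 | 0.1210 | 0.1213 |
| 2 and 1.5 | 0.725 | 0.718 | 0.1215 | 0.1219 |
| 3 and 2 | 0.731 | 0.713 | 0.1223 | 0.1228 |

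Each mean hazard ratio carries a simulation error of about 0.12/√1000 × 0.72 = 0.003. Entering the factors as covariates instead of strata gave nearly the same results (0.718, 0.717 and 0.713). The standard error hardly moves; the loss comes through the hazard ratio shifting toward 1.

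**The case against.** Several counter-arguments stand.

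- The stratified analysis is already pre-specified, with both factors and the cut-point named, so the proposal mainly reverses the order of two planned analyses.
- The sample size rests on a log-rank test with no stratification mentioned, so the lead analysis matches the design calculation.
- Only previous episodes is called prognostic; the plan does not say so of recruitment source. The 5-point loss needs hazard ratios of 3 and 2, which nothing in the plan supports.
- Part of the shift in the hazard ratio is a difference of estimand, because marginal and conditional hazard ratios are not the same quantity.
- It would be too strong to say that the imbalance rule can never admit these factors. Only the two-level split is balanced by design, whereas the baseline table reports previous episodes as a mean, which can differ within strata.

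A reader might go further than the document allows in three ways.

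- **That the primary test is invalid.** It is not: the unstratified type I error was 4.1% to 4.7%, below the nominal level.
- **That precision is lost.** The model standard errors are almost identical, so the loss is in power.
- **That there are two rival primary results and no rule for choosing.** The wording reads more naturally as a lead model followed by an additional check. The label could be clearer, and interpretation is to take place on masked data.

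None of this is a reason to keep a prognostic stratification factor out of the lead model.

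**Conclusion.** The point holds as a modest improvement and is not a flaw in validity. The lead Cox model omits both randomisation factors, the imbalance rule would almost never admit them, and no other section puts them in. The cost is roughly 0 to 1.6 points of power for assumed factor hazard ratios of 1 to 2, and about 5 points for 3 and 2, with a slightly conservative test and a hazard ratio a little closer to 1. These sizes depend on stratum shares and prognostic hazard ratios that the plan does not give. The direction does not depend on the exact values, provided at least one factor is prognostic, as the plan says of previous episodes.

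**What to change.** In the Primary analysis section, name one primary model: a Cox regression stratified by, or adjusted for, previous episodes (up to 2 versus more than 2) and recruitment source (community versus clinician), and state which of the two forms is used. If a log-rank p-value is reported, use the matching stratified version. Label the unstratified Cox model a sensitivity analysis. State that the same applies to any recurrence and care-seeking recurrence. The economic models would then take over both factors through the existing cross-reference.

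The cost is wording only. Both factors were needed to randomise, so they should be on record for every participant, and the required 698 participants and 279 events do not change. The change should be made before database lock and unmasking.

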#### Secondary analyses

##### Effectiveness outcome analyses

For the outcomes of *any LBP recurrence* or a *care-seeking recurrence of LBP*, an analogous survival analysis to that of the primary outcome detailed above will be conducted.

To test the effects of the intervention on continuous secondary outcomes, between-group comparisons will be conducted using multiple linear mixed-effects regression combining all available post-randomisation measurements (at either months 3, 6, 9 or 12 depending on outcome collection). Transformations will be applied to meet model assumptions, if needed. Linear mixed modelling will be used to take account of the correlation between measurements within an individual for repeated measurements over time. A template has been provided for how the data will be reported (see Table 2).

**Table 2 Tab2:** Secondary outcomes

	**Intervention (*****n***** = xxx)**	**Control (*****n***** = xxx)**	**Mean difference (95% CI), *****p*****-value**
Disability—RMDQ			
Month 3	xx.x (SD), *n*	xx.x (SD), *n*	xx.x (xx.x to xx.x),* p* = 0.xxx
Month 6	xx.x (SD), *n*	xx.x (SD), *n*	xx.x (xx.x to xx.x),* p* = 0.xxx
Month 9	xx.x (SD), *n*	xx.x (SD), *n*	xx.x (xx.x to xx.x),* p* = 0.xxx
Month 12	xx.x (SD), *n*	xx.x (SD), *n*	xx.x (xx.x to xx.x),* p* = 0.xxx
Health-related QoL – EQ-5D-5L			
Month 3	xx.x (SD), *n*	xx.x (SD), *n*	xx.x (xx.x to xx.x),* p* = 0.xxx
Month 6	xx.x (SD), *n*	xx.x (SD), *n*	xx.x (xx.x to xx.x),* p* = 0.xxx
Month 9	xx.x (SD), *n*	xx.x (SD), *n*	xx.x (xx.x to xx.x),* p* = 0.xxx
Month 12	xx.x (SD), *n*	xx.x (SD), *n*	xx.x (xx.x to xx.x),* p* = 0.xxx
Self-reported Physical Activity—IPAQ			
Month 3	xx.x (SD), *n*	xx.x (SD), *n*	xx.x (xx.x to xx.x),* p* = 0.xxx
Month 12	xx.x (SD), *n*	xx.x (SD), *n*	xx.x (xx.x to xx.x),* p* = 0.xxx
ActiGraph measure at 3 months^a^			
Steps per day	xx.x (SD), *n*	xx.x (SD), *n*	xx.x (xx.x to xx.x),* p* = 0.xxx
Brisk Steps per day^b^	xx.x (SD), *n*	xx.x (SD), *n*	xx.x (xx.x to xx.x),* p* = 0.xxx
MVPA minutes per day	xx.x (SD), *n*	xx.x (SD), *n*	xx.x (xx.x to xx.x),* p* = 0.xxx

*EQ-5D-5L* EuroQol 5-Dimension 5-Level, *IPAQ* International Physical Activity Questionnaire, *MVPA* Moderate-vigorous physical activity, *RMDQ* Roland-Morris Disability Questionnaire

^a^Data in above table represents a minimum 4-day, and maximum of 7-day wear period. Only data for participants whose dataset met the minimum wear time requirement of 10 h/day are included

^b^Brisk walking is defined as a cadence > 100 steps per minute

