## Background

Low back pain (LBP) is the mostprevalent musculoskeletal condition worldwide and has been the leading cause of years lived with disability over the past three decades [1]. Isolated episodes of non-specific LBP have a favourable prognosis [2], but LBP is often recurrent with approximately 70% of individuals experiencing a new episode within 12 months following recovery [3]. Exercise appears to prevent recurrences of LBP and work-related absenteeism; however, few large-scale trials have examined scalable exercise interventions which are both accessible and affordable to recurrent LBP sufferers [4–6].

The WalkBack trial is a pragmatic, parallel-group, randomised controlled trial (RCT) investigating the effectiveness and cost-effectiveness of a progressive and individualised walking and education program compared to a no-treatment control group, in reducing recurrences of LBP. The protocol for the study has been published elsewhere and an internal protocol exists (version 4.1) [7]. Recruitment concluded in June 2022 and 701 participants were randomised to either the intervention (walking and education program) or a no-treatment control group (usual care). Provision of the intervention period (6 months) concluded in December 2022 and the final follow-up of outcome data will conclude in June 2023. Here, we describe the statistical analysis plan to guide data analyses for the trial and outline planned future supplementary analyses. Final statistical analysis will be performed following the completion of data collection, integrity checks and database lock (estimated September 2023).

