##### Secondary effectiveness outcomes

*Any LBP recurrence*is defined as a return of LBP lasting at least 24 h with a pain intensity > 2 (0–10 Numeric Pain Rating Scale). This is the lowest recurrence threshold to define any new episode of recurrence [9].*Care-seeking LBP recurrence is* defined as a return of LBP lasting at least 24 h with a pain intensity > 2 (0–10 Numeric Pain Rating Scale) leading to care-seeking with a healthcare provider (e.g. GP, physiotherapist, chiropractor, massage therapist, and acupuncturist).*Disability*will be measured by the Roland-Morris Disability Questionnaire (RMDQ) collected quarterly across 12 months [10].*Health-related quality of life*will be measured by the EuroQol 5-Dimension 5-Level (EQ-5D-5L) questionnarie collected quarterly across 12 months, and valued using the Canadian tariff [11, 12].

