#### Baseline participant characteristics

Baseline characteristics will be presented separately for each arm of the trial. Data collected from the baseline questionnaire including age, gender, work and educational status, and relevant history of back pain will be presented in a table. The full list of baseline characteristics and demographics that will be reported is presented in Table 1.

**Table 1 Tab1:** Baseline characteristics of participants

	**Intervention (*****n***** = xxx)**	**Control (*****n***** = xxx)**
Female	*n*/*N* (%)	*n*/*N* (%)
Age (years)	xx.x (SD), *n*	xx.x (SD), *n*
BMI (kg/m^2^)	xx.x (SD), *n*	xx.x (SD), *n*
Education level		
Some secondary school	*n*/*N* (%)	*n*/*N* (%)
Completed secondary school	*n*/*N* (%)	*n*/*N* (%)
Some additional training	*n*/*N* (%)	*n*/*N* (%)
Undergraduate university	*n*/*N* (%)	*n*/*N* (%)
Postgraduate university	*n*/*N* (%)	*n*/*N* (%)
Current work status		
Full-time	*n*/*N* (%)	*n*/*N* (%)
Part time	*n*/*N* (%)	*n*/*N* (%)
Unemployed	*n*/*N* (%)	*n*/*N* (%)
Students or homeworkers	*n*/*N* (%)	*n*/*N* (%)
Sick leave or pension	*n*/*N* (%)	*n*/*N* (%)
Retired	*n*/*N* (%)	*n*/*N* (%)
Other	*n*/*N* (%)	*n*/*N* (%)
Gross weekly household income (annual in brackets)		
No income	*n*/*N* (%)	*n*/*N* (%)
$1–$649 ($1–$33,799)	*n*/*N* (%)	*n*/*N* (%)
$650–$1699 ($33,800–$88,399)	*n*/*N* (%)	*n*/*N* (%)
$1700–$3999 ($88,400–$207,999)	*n*/*N* (%)	*n*/*N* (%)
$4000 or more ($208,000 or more)	*n*/*N* (%)	*n*/*N* (%)
Smoking status		
Never	*n*/*N* (%)	*n*/*N* (%)
Current smoker	*n*/*N* (%)	*n*/*N* (%)
Ex-smoker	*n*/*N* (%)	*n*/*N* (%)
Manual task involving heavy loads		
Very frequently	*n*/*N* (%)	*n*/*N* (%)
Frequently	*n*/*N* (%)	*n*/*N* (%)
Occasionally	*n*/*N* (%)	*n*/*N* (%)
Rarely	*n*/*N* (%)	*n*/*N* (%)
Very rarely	*n*/*N* (%)	*n*/*N* (%)
Never	*n*/*N* (%)	*n*/*N* (%)
Manual task involving awkward positions		
Very frequently	*n*/*N* (%)	*n*/*N* (%)
Frequently	*n*/*N* (%)	*n*/*N* (%)
Occasionally	*n*/*N* (%)	*n*/*N* (%)
Rarely	*n*/*N* (%)	*n*/*N* (%)
Very rarely	*n*/*N* (%)	*n*/*N* (%)
Never	*n*/*N* (%)	*n*/*N* (%)
General health		
Excellent	*n*/*N* (%)	*n*/*N* (%)
Very good	*n*/*N* (%)	*n*/*N* (%)
Good	*n*/*N* (%)	*n*/*N* (%)
Fair	*n*/*N* (%)	*n*/*N* (%)
Poor	*n*/*N* (%)	*n*/*N* (%)
Low back pain		
Previous episodes	xx.x (SD), *n*	xx.x (SD), *n*
Duration of last episode (days)	xx.x (SD), *n*	xx.x (SD), *n*
Time since last episode (days)	xx.x (SD), *n*	xx.x (SD), *n*

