Perceived risk of recurrence (0 to 10)	xx.x (SD), *n*	xx.x (SD), *n*
Levels of physical activity (IPAQ)		
Walking (min/week)	xx.x (SD), *n*	xx.x (SD), *n*
Moderate (min/week)	xx.x (SD), *n*	xx.x (SD), *n*
Vigorous (min/week)	xx.x (SD), *n*	xx.x (SD), *n*
Time sitting (min in average weekday)	xx.x (SD), *n*	xx.x (SD), *n*
DASS-21 (0 to 21)		
Depression	xx.x (SD), *n*	xx.x (SD), *n*
Anxiety	xx.x (SD), *n*	xx.x (SD), *n*
Stress	xx.x (SD), *n*	xx.x (SD), *n*
Sleep quality		
Very good	xx.x (SD), *n*	xx.x (SD), *n*
Fairly good	xx.x (SD), *n*	xx.x (SD), *n*
Fairly bad	xx.x (SD), *n*	xx.x (SD), *n*
Very bad	xx.x (SD), *n*	xx.x (SD), *n*
Health Status (Euro-QOL)		
EQ-5D-5L Health State Index	xx.x (SD), *n*	xx.x (SD), *n*
EQ-VAS score (0–100)	xx.x (SD), *n*	xx.x (SD), *n*

*BMI* Body mass index, *DASS-21* Depressions Anxiety Stress Scale, *EQ-5D-5L* EuroQol 5-Dimension 5-Level, *IPAQ* International Physical Activity Questionnaire, *VAS* Visual analogue scale, *QOL* Quality Of Life, *kg* kilogram, *m* metre, *SD* Standard Deviation

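### The mixed model for EQ-5D-5L names no baseline term, although the baseline index is collected and the QALY analysis uses it

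*SAP article*

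**What the plan says.** Under Effectiveness outcome analyses, the SAP article specifies that "between-group comparisons will be conducted using multiple linear mixed-effects regression combining all available post-randomisation measurements", with visits "at either months 3, 6, 9 or 12 depending on outcome collection". The section mentions within-person correlation and possible transformations. It lists no covariates. Table 2, the reporting template, gives EQ-5D-5L at months 3, 6, 9 and 12, with a mean difference, confidence interval and p-value at each visit and no baseline row.

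Three other places bear on this:

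- **Baseline participant characteristics.** The article says "The full list of baseline characteristics and demographics that will be reported is presented in Table 1". That table includes "EQ-5D-5L Health State Index", so the baseline value exists. It also includes baseline IPAQ minutes, but no RMDQ and no accelerometer row.
- **Economic evaluation analyses.** Cost and effect differences use the covariates of the primary effectiveness analyses, "in addition to work status and baseline utility values for QALYs".
- **Physical activity data analyses.** IPAQ is compared by linear regression at baseline, month 3 and month 12. Baseline is one of the timepoints compared; it is not named as a covariate for the later ones.

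**The concern.** In a randomised trial the baseline value of a continuous outcome is usually one of the strongest predictors of its later values. Leaving it out does not bias the comparison, but it has two costs. The residual variance stays larger than it need be, so confidence intervals are wider. A chance difference between arms at baseline also carries through in part to the follow-up difference, with nothing in the model to remove it.

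Here the plan already recognises the value of this covariate. It adjusts the 12-month utility summary (QALYs) for baseline utility but says nothing of the kind for the visit-level values of the same instrument. Health-related quality of life is listed among the key secondary outcomes in the abstract, so the analysis should be as efficient as the collected data allow, and the baseline term should be fixed before the data are seen.

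**Working it through.** **Is there a figure of the plan's own to reproduce?** Not for the continuous outcomes: the article gives no SD, target difference or precision for them. Its only sample-size statement, that "349 participants per group (698 total) would provide 80% power to detect a 25% relative reduction in recurrence rates", concerns the log-rank test. It does reproduce:

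- The 12-month risks of 30% and 22.5% give a hazard ratio of ln(0.775)/ln(0.70) = 0.715.
- Schoenfeld's formula then needs 4 × (1.960 + 0.842)² / (ln 0.715)², or 279 events.
- With uniform accrual over 24 months, 12 further months of follow-up and 1% monthly loss, the event probabilities are 0.449 and 0.351 (mean 0.400), and 279/0.400 gives 698.

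That calculation is sound and does not bear on this point.

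**Inputs for the check.**

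- Number per arm: about 350, since "701 participants were randomised to either the intervention (walking and education program) or a no-treatment control group (usual care").
- Baseline-to-follow-up correlation r: not in the article. Assumed over 0.2 to 0.6.
- Outcome SD: not in the article. Results are in SD units.
- Illustrative difference for power: 0.2 SD, an assumption.

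**Formulas, for a difference at one visit (which is what Table 2 reports).**

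- Unadjusted SE = √(2/350) = 0.0756 SD.
- Baseline-adjusted SE = 0.0756 × √(1 − r²). The variance falls by the fraction r².
- Equivalent gain in participants = 1/(1 − r²) − 1.
- Power = Φ(0.2/SE − 1.96).

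| r | SE (SD units) | Variance cut | Equivalent extra participants | Power for 0.2 SD |
|---|---|---|---|---|
| no adjustment | 0.0756 | – | – | 75.4% |
| 0.2 | 0.0741 | 4% | 4% | 77.0% |
| 0.3 | 0.0721 | 9% | 10% | 79.2% |
| 0.4 | 0.0693 | 16% | 19% | 82.3% |
| 0.5 | 0.0655 | 25% | 33% | 86.3% |
| 0.6 | 0.0605 | 36% | 56% | 91.1% |

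If 12% had no value at a visit (308 per arm, an assumption), unadjusted power would be 69.9%, against 74.0% at r = 0.3 and 81.8% at r = 0.5. The proportional variance cuts do not change.

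**Chance imbalance.** A baseline difference of d SD between arms shifts the unadjusted follow-up difference by about r × d. An imbalance of two standard errors is 2 × 0.0756 = 0.151 SD. At r = 0.5 it moves the follow-up estimate by 0.076 SD, one full standard error of that estimate. At r = 0.2 it moves it by 0.030 SD. Adjustment removes this component.

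**Which outcomes qualify.**

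| Outcome | Baseline value shown | Planned model | Baseline term named |
|---|---|---|---|
| EQ-5D-5L | Yes, Table 1 | Mixed model, months 3 to 12 | No |
| IPAQ | Yes, Table 1 | Linear regression by timepoint | No; baseline is a comparison timepoint |
| RMDQ | No | Mixed model, months 3 to 12 | Not applicable on what is shown |
| ActiGraph | No, month 3 only | Linear regression at month 3 | Not applicable |

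**The case against.** The strongest defence is that the text is silent and does not exclude adjustment. The phrase about post-randomisation measurements says which outcome values enter the model, and a model with follow-up values as response and baseline as covariate could be described the same way. The word multiple in the model's name hints at covariates, and the article refers to a published protocol and an internal one that may list them. This stands to the extent that the point is an unnamed term, not a stated refusal to adjust. It does not remove the point: the article is itself the analysis plan, it names covariates for the QALY regression, and the provision to adjust for unbalanced prognostic factors is written for recurrence and carried over only to the other recurrence outcomes.

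The second defence is that r may be low. Recovery at entry required more than 7 consecutive days with pain no greater than 1, so baseline utility may cluster near its ceiling and predict later values weakly. This stands, and is why the assumed range starts at 0.2. It is only partial, because EQ-5D-5L measures general health and recovery was defined by back pain alone. Baseline IPAQ may be restricted in the same way, since the entry criteria exclude people who are already active.

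Several stronger readings are tempting but unsupported:

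- *All the continuous outcomes are affected.* No baseline is shown for RMDQ or ActiGraph.
- *Table 2 reports raw differences.* It says only mean difference and is the template for the model results.
- *The QALY and quality-of-life results could disagree solely because of the missing covariate.* They also differ in estimand (area under the curve against visit-specific means), imputation, joint modelling with costs, and other covariates. Where baseline utility is the first point of the area under the curve, there is also a separate reason to adjust QALYs.
- *The gain is 29% to 51%.* That applies to a four-visit average under compound symmetry with r of 0.4 to 0.6, which Table 2 does not report. If baseline correlates 0.3 with follow-up and follow-ups correlate 0.6 with each other, the cut is 0.09/0.70, about 13%.

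**Conclusion.** The point holds for EQ-5D-5L, as a free improvement to a secondary analysis. The plan collects the baseline index, uses baseline utility for QALYs, and names no baseline term in the mixed model for the same instrument. As written, each visit-specific difference would carry a variance that adjustment could cut by about 4% to 36%, for an assumed correlation of 0.2 to 0.6. The true correlation is not in the article and may lie towards the low end.

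A reader might infer that the planned estimate is biased or its test invalid. It is neither: the unadjusted randomised comparison is valid, and about 350 per arm limits the likely imbalance. The loss is one of precision and of protection against chance imbalance. The same reasoning applies to IPAQ at months 3 and 12, within its own linear regressions. The primary time-to-event analysis is unaffected.

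**What to change.** - In Effectiveness outcome analyses, state that the EQ-5D-5L mixed model includes the baseline index, with baseline-by-visit and arm-by-visit terms. It can enter as a covariate, or as a response with the arm means constrained equal at baseline. The constrained form also keeps participants whose baseline value is missing.
- In Table 2, label the EQ-5D-5L differences as baseline-adjusted.
- In Physical activity data analyses, use baseline IPAQ as a covariate in the month 3 and month 12 regressions, and label those differences in the same way.
- If the protocol already lists these covariates, repeat them here so that the plan is complete on this point.

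The cost is a few sentences and one or two extra model terms. No new data are needed, and the change can be made before the database lock, which the article estimates for September 2023.
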